#### Physiotherapy exercises

A standardised physiotherapy exercise intervention has been developed based on a systematic literature review and meetings with clinical physiotherapists working in the field to combine evidence and practical experience. The process of developing the intervention and the intervention itself are presented in a separate publication ([name] et al., in prep). The programme is described in a detailed manual that presents the exercises, the number of repetitions at each training level, and criteria for progression.

Depending on their need for supervision, the patients attend a physiotherapist at a municipal training centre 8–15 times within a period of eight weeks, including an initial and a final clinical evaluation. The physiotherapist-supervised individual training sessions last up to 60 minutes each. The patients are instructed to perform additional self-training. At baseline, advice is given on general physical activity, questions concerning analgesics are transferred to the patient’s general practitioner, and the patient is advised to refrain from other specific shoulder training during the intervention period. The patient keeps a self-training diary, and the physiotherapist registers any deviations from the manual and scores patient adherence. Any adverse events are noted.

#### Occupational medical assistance and physiotherapy exercises

This entails a combination of the two interventions described above.

### Usual care and co-interventions

At three month follow up, questionnaire information is collected about non-surgical treatment in terms of number of treatments by physiotherapists, physicians, chiropractors, and other health care providers, types of treatment (shoulder training, subacromial injections, manual therapy, and shock wave therapy), use of analgesics, work modifications due to the operated shoulder, job centre initiated workplace visits, and any advice to stop working or find other employment given from whom, see Table 1.

### Primary outcome measures

To evaluate the physiotherapy intervention at three months, the primary outcome measure will be change in shoulder function since baseline assessed by *Oxford Shoulder Score* (OSS), which ranges from 0 to 48 with 48 being the best outcome [29]. To evaluate the occupational intervention at three months, the primary outcome measure will be the *sickness absence percentage*, i.e. the number of hours of sick-leave due to symptoms from the operated shoulder in relation to the number of planned working hours within three months from baseline. This information is gathered by one month day-by-day calendars. Any hours off work to participate in the project will count in the outcome measure.

To evaluate the physiotherapy intervention at 12 months, the primary outcome measure will be *OSS.* For the subgroup, who are in paid work for at least 25 hours per week, the occupational intervention will be evaluated at 12 and 24 months, and the physiotherapy intervention will be evaluated at 24 months, using the primary outcome measure *transfer income percentage*, i.e. the number of weeks receiving temporary or permanent health-related transfer incomes within 12 and 13–24 months from baseline, respectively, divided by 52 weeks, according to the Danish National Register on Public Transfer Payments [30].

As a consequence of the change of inclusion criteria, we had to change the intended primary outcome measures for the occupational intervention at 3 and 12 months. The original measures at these follow up occasions were duration of fulltime sick-leave and duration of sick-leave until lasting return to work, respectively.

### Secondary and supplementary outcome measures

At three months, *Constant Score* will be used as a secondary outcome measure for the physiotherapy intervention [31-33], and *OSS* will be used as a secondary outcome measure for the occupational intervention to evaluate any deterioration. For both interventions, the *Fear Avoidance Belief Score*[34], modified to focus on the shoulder [35] will also be used. Furthermore, the physiotherapy intervention will be evaluated using the *sickness absence percentage* for the subgroup in paid work for at least 25 hours per week.

At 12 months, the *Fear Avoidance Belief Score*, modified to focus on the shoulder, will be used as a secondary outcome measure for both interventions, and *OSS* will be used as a secondary outcome measure for the occupational intervention. For the subgroup, who are in paid work for at least 25 hours per week, the physiotherapy intervention will be further evaluated using the *transfer income percentage.*

For both interventions, supplementary outcome measures will be chosen from the variables presented in Table 1. As an annex to the RCT, participants are asked to answer a short text message once a week for 12 weeks after baseline, rating their pain at rest within the last 24 hours, using an 11-point Numeric Pain Rating Scale ranging from 0 (no pain) to 10 (worst imaginable pain).

### Randomisation

At the region’s two departments of occupational medicine, participants are individually randomised by a research secretary, using a computerised random number generator with stratification by surgical department and blocking within strata using randomly permuted block sizes of 12, 8, and 4. Blocking within strata is used to ensure an equal distribution of the interventions between the surgical departments. Randomly permuted block sizes ensure allocation concealment. Once performed, the randomisation result is automatically locked by SIP-online (see below).

### Data collection and blinding

All project activities are documented in a web-based data management system, SIP-online (Trial Partner®), tailored to the project. SIP-online is password protected, and data is transferred via secure lines (https) to a server protected by firewalls. Data is backed up every 24 hours. After closure of the project, data will be stored at the Danish Data Archives.

Before randomisation and at 3 month follow up, shoulder examination and physical testing is performed by a research physiotherapist. At 3 months, blinding of the research physiotherapist for group assignment is ensured by restricted access to SIP-online and instructions to the participants not to tell him about their group assignment. The success of blinding of the outcome assessor will be evaluated.

### Process evaluation

The degree to which the project reaches the targeted group of patients will be assessed by comparing the RCT group with other patients from the cohort with respect to *OSS*, *full return to own or other work with equal earnings*, and *transfer income percentage* within specified time periods after surgery.

For the occupational intervention, process evaluation will include the timeline of the process as compared to the protocol, the number of workplace visits in relation to the number indicated, and the degree to which planned workplace adaptations are implemented (a score from 0 to 10). For the physiotherapy intervention, adherence to the protocol will be evaluated in terms of the percentage of participants where the minimum number of supervised training sessions is completed, the percentage of participants where deviations from the training protocol are registered, and the percentage of participants who – according to their training diary - perform self-training with the advised frequency.

Participant preferences with respect to intervention group [36], and satisfaction with participation in SIP are covered by questionnaires at baseline and three month follow up, respectively, as shown in Table 1.

### Statistical analyses

Trial results will be reported as a summary of the outcome measures in each group together with the estimated effect size and its precision. Statistical analyses will be performed according to the intention-to-treat principle, which will be supplemented by per protocol analyses depending on the proportion who do not receive the intended treatment. For outcomes measured using an essentially continuous scale (e.g. *OSS, sickness absence percentage,* and *transfer income percentage*), differences between groups at follow up will be compared by means of linear regression modelling with appropriate transformation of dependent variables. Analyses of effects of the physiotherapy intervention will be adjusted for centre (department of occupational medicine), for the occupational intervention (no, yes, irrelevant), and for the outcome measure at baseline. For the subgroup, who are in paid work for at least 25 hours per week, a two-by-two factorial design will be used. The analyses will focus on main effects of the occupational intervention, but cell-by-cell results will also be reported [22,23]; the analyses will be adjusted for centre. Numbers needed to treat for one patient to benefit from the interventions will be calculated [37]. In addition to main RCT results, supplementary analyses will be performed using variables presented in Table 1.

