## Methods/Design

### Design and setting

The study is a mainly pragmatic multicentre RCT [21]. The RCT is embedded in a cohort study, which comprises all patients aged ≥18–≤63 years who are referred to one of six public departments of orthopaedic surgery in Central Denmark Region on suspicion of SIS in a three year period, 2011–2014. Figure 1 presents the inclusion of patients and the stages of the RCT. The physiotherapy intervention will be evaluated for patients with and without paid work. The occupational intervention (and the physiotherapy intervention) will be evaluated for the subgroup of patients, who have paid work for at least 25 hours per week, using a factorial design [22,23]. Table 1 presents variables in the RCT and in the cohort study, in which the RCT is embedded.

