## Discussion

The few studies that have compared the effect of different postoperative exercise programmes have focussed on the initial 4–12 weeks and have targeted all patients after decompression surgery for SIS [13-16]. We chose to start our interventions 8–12 weeks after surgery, where the six orthopaedic departments that contribute patients to SIP routinely schedule postoperative control, and where we thought that we would be able to target our efforts on the subgroup of patients with continuing shoulder problems and an increased likelihood of chronic disability. Any problems regarding work retention would also be crystallised at this time, where unrestricted activities are usually allowed.

The RCT is embedded in a cohort study, which enables evaluation of selection into the project and reach of the intended target group. It is impossible to blind participants and providers of the interventions. To minimise information bias, we included register-based variables and Constant Score as outcome measures and aimed to ensure blinding of the research physiotherapist. Diagnostic practice, preoperative treatment, indications for surgery, and early postoperative training are not standardised, but preoperative treatment and early postoperative training is described by means of questionnaire data. Moreover, preoperative OSS is assessed, which also ensures that comparability with patients from other settings can be judged.

Results of SIP can be incorporated into clinical practice guidelines for rehabilitation after arthroscopic decompression for SIS. If the interventions are successful, information materials will be prepared for use in hospital departments, primary health care, job centres, and training centres, including job-title-based red-yellow-green charts to guide health care professionals and social workers regarding the need for occupational medical assistance. SIP evaluates a new rehabilitation approach, where physiotherapy and occupational interventions are provided in continuity of surgical episodes of care. If successful, the project may serve as a model for rehabilitation of surgical shoulder patients.

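### The randomisation strata (six surgical departments) are absent from the stated primary models, which adjust for the two departments of occupational medicine: no bias, but slightly conservative inference

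*Protocol article*

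**What the plan says.** **Allocation (Randomisation).** Participants are individually randomised "with stratification by surgical department and blocking within strata using randomly permuted block sizes of 12, 8, and 4". The purpose is stated: "Blocking within strata is used to ensure an equal distribution of the interventions between the surgical departments".

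**Number of strata.** Design and setting describes patients "referred to one of six public departments of orthopaedic surgery in Central Denmark Region". The Discussion again refers to "the six orthopaedic departments that contribute patients to SIP".

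**Departments of occupational medicine.** Randomisation is carried out at the region's "two departments of occupational medicine, participants are individually randomised by a research secretary". They are named as the place where allocation happens, not as a stratification factor.

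**Analysis (Statistical analyses).** The method is linear regression. Physiotherapy analyses "will be adjusted for centre (department of occupational medicine"), for the occupational intervention (three categories) and for the baseline value of the outcome. The two-by-two factorial analyses in the employed subgroup are adjusted for *centre*, which is not defined again. Surgical department is not listed as a covariate in any analysis.

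**The concern.** The design balances the arms on one factor and the analysis adjusts for a different, coarser one. Blocking within departments makes the arms more alike than simple randomisation would. The usual regression standard error reflects that gain only if the blocking factor is in the model. When it is left out, between-department variation stays in the residual although it has largely been removed from the treatment comparison. The standard error is then too large, the interval too wide and the test below its nominal size.

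The protocol gives some reason to think departments could differ. Its Discussion says that diagnosis, treatment before surgery, the indications for operating and early training afterwards were not standardised. The sponsor also thought department important enough to stratify on. At stake is the accuracy of the precision that the trial promises to report, and a little power.

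**Working it through.** **Step 1. Does the analysis factor match the stratum?**

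| Item | Factor | Levels | Section |
|---|---|---|---|
| Stratum | Surgical department | 6 | Randomisation; Design and setting; Discussion |
| Covariate, physiotherapy models | Department of occupational medicine | 2 | Statistical analyses |
| Covariate, factorial models | *Centre*, not redefined | 2, by the only definition given | Statistical analyses |

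They do not match. For the physiotherapy models this is explicit. For the factorial models it follows from the single definition, given in the same paragraph.

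**Step 2. Reproduce the plan's baseline figure.** Sample size calculations gives 50 per group, a detectable difference of 11.9 percentage points in sickness absence, SD 20, power 0.80, alpha 0.05 (taken as two-sided) and 10% dropout.

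- n per group = 2 × (1.960 + 0.842)² × 20² / 11.9² = 2 × 7.849 × 400 / 141.61 = 44.3, so 45 evaluable.
- 45 / 0.90 = 50 recruited per group.
- Power at 45 per group is 0.806.

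The figure reproduces, so 90 evaluable patients is a fair base for the next steps.

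**Step 3. Approximate size of the effect.** Let ICC be the share of residual variance lying between surgical departments and not captured by the two-level term. The documents do not give it, so a range is assumed. With near-perfect balance, the standard error is overstated by 1/√(1 − ICC), and the actual size is 2 × [1 − Φ(1.96 × ratio)].

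- ICC 0.05: ratio 1.026, size 0.044.
- ICC 0.10: ratio 1.054, size 0.039.

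**Step 4. Simulation of the planned setting.** Assumptions: two-by-two factorial, 90 evaluable patients, six equal departments, permuted blocks of 4, 8 and 12 within department, total SD 20, normal outcome, linear regression, 6,000 runs per setting. Departments are assumed nested three and three in the two occupational centres. Here ICC is the share of total variance between departments. Monte Carlo standard errors are about √(0.8 × 0.2 / 6000) = 0.005 for power and √(0.05 × 0.95 / 6000) = 0.003 for size.

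| Assumed ICC | Power, 2-level centre | Power, 6 departments | Type I error, 2-level | Type I error, 6 departments |
|---|---|---|---|---|
| 0 | 0.800 | 0.795 | 0.046 | 0.047 |
| 0.02 | 0.798 | 0.801 | 0.050 | 0.052 |
| 0.05 | 0.808 | 0.816 | 0.045 | 0.048 |
| 0.10 | 0.807 | 0.827 | 0.045 | 0.052 |
| 0.20 | 0.836 | 0.878 | 0.033 | 0.048 |

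At ICC 0.20 with no true effect, the two-level model reports a mean standard error of 4.08 against an actual SD of the estimate of 3.78 (ratio 1.08). The six-level model reports 3.78 against 3.74 (ratio 1.01). The effect is milder than Step 3 suggests because the two-level term absorbs some of the department variance and because 15 patients per department leave the last block incomplete.

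**Step 5. Cost in degrees of freedom.** Going from two levels to six uses 4 more. Residual degrees of freedom fall from 90 − 4 = 86 to 82 in the factorial model. In the physiotherapy model, with 130 × 0.90 = 117 evaluable, they fall from 117 − 6 = 111 to 107. If both factors are kept and are not nested, the cost is 5.

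**The case against.** The strongest reply is that the effect is small and errs in the safe direction. Blocking already delivers the balance that the protocol wanted, the estimate is unbiased and no excess of false positives arises. Up to an ICC of 0.05 the difference in power is within about 1 point. Only at 0.20 is it plain. This stands, and it sets the weight of the point.

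The size also rests on an assumption. Saying that care was not standardised is not saying that outcomes differ by department. The physiotherapy models adjust for the baseline outcome, measured after surgery, which may absorb part of any department difference. This stands too, and is why the range starts at zero. The baseline argument is weaker for the factorial models, where centre is the only adjustment named.

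Three stronger readings are tempting and not supported:

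- A reader might infer that the trial cannot afford any loss because it is already short of power. The occupational calculation reproduces at 0.806, so that is not shown here. The Oxford Shoulder Score calculation is a separate question.
- A reader might infer that every primary model explicitly omits the stratum by naming another factor. For the factorial models this is the natural reading of *centre*, not an explicit statement.
- A reader might infer that department of occupational medicine should simply be swapped out. The protocol does not say whether surgical departments are nested in the two occupational departments. If they are not, a swap would drop a planned adjustment. Trial status also says that the 3-month physiotherapy analysis is under way, so changing its primary model is more than a wording edit.

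An unseen analysis plan is not an answer to the mismatch itself, because the article states its covariates and defines centre.

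**Conclusion.** The point holds as an inconsistency between design and analysis with a modest, conservative consequence. The stratification factor is absent from the stated primary models: explicitly for physiotherapy, and by the only available definition for the factorial models.

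The treatment estimate is not biased. The loss is about 0–2 points of power if departments hold 0–10% of the variance. At 20% it is about 4 points, with type I error about 0.033. These figures rest on an assumed variance share, equal department sizes, normal outcomes and three-and-three nesting, none of which the documents give. Confidence is high in the mismatch and limited in its size. The change is still worth making, because it costs about half a power point if departments do not differ at all (0.800 to 0.795).

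**What to change.** Add surgical department to all primary models as a six-level fixed effect, pooling only departments with very few patients. Keep department of occupational medicine alongside it, or let surgical department take its place if the surgical departments are nested in the two occupational ones; state which applies. Say that *centre* in the factorial models means the same as in the physiotherapy models.

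For the 3-month physiotherapy analysis, make the change before any results by arm have been seen. Otherwise keep the published model as primary and report the surgical-department model as a declared sensitivity analysis. The later analyses can be specified prospectively.

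The cost is about 4 degrees of freedom with 90 to 117 evaluable patients, a short text change and a dated note of the reason. No new data are needed, since surgical department is already held for randomisation.

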**Questionnaire**							
Job title	x	x	x	x	x	x	
Psychosocial working environment			x				
Work ability	x	x	x	x	x	x	
Work productivity and activity impairment				x	x		
Work modifications				x			
Advice to stop working				x			
Job centre initiated workplace visits				x			
Compensation claims	x		x				
Oxford Shoulder Score	x	x	x	x	x	x	
Shoulder pain intensity			x	x	x		
Duration of shoulder symptoms	x	x					
Global impression of change			x (since shortly before surgery)	x (since baseline)	x (since assessment at 3 months)		
Other musculoskeletal complaints		x	x		x		
EQ-5D-3L*	x	x	x	x	x	x	
Use of analgesics		x	x	x	x		
Non-surgical treatment		x (previous 3 months)	x (since operation)	x (previous 3 months)	x (previous 3 months)	x (previous 3 months)	
Expectations to surgery		x			x (fulfilment)		
Patient preferences			x				
Height, weight, handedness		x					
Smoking		x					
Physical activity		x	x	x	x		
Fear avoidance beliefs			x	x	x		
Self efficacy			x				
Mental health		x	x	x	x		
Satisfaction with SIP*				x			
Shoulder-related sickness absence				x			
Full return to own or other work with equal earnings					x	x	

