### Participants

To be included in the RCT, patients must have surgery under a main diagnosis of SIS or acromioclavicular osteoarthritis (International Classification of Diseases 10^th^ revision: M75.1-M75.8 or M19) and with a main shoulder surgery code of arthroscopic subacromial decompression (KNBH51, KNBH91, KNBG09, KNBL39, or KNBM79 according to the Danish version of the Nordic Medico-Statistical Committee Classification of Surgical Procedures). Exclusion criteria are shown in Figure 1. At postoperative clinical control after 8–12 weeks, eligible patients are provided with information material on SIP and are asked to participate in a brief telephone interview. Patients are only recruited if they have at least slight shoulder problems doing usual activities (e.g. work, study, housework, family or leisure activities) when assessed on a five level scale (no problems, slight problems, moderate problems, severe problems, unable). Furthermore, the patients’ employment status is assessed. Patients can be randomised to one of all four arms of the RCT if they are in paid work for at least 25 hours per week. Remaining patients can only be randomised to one of the two arms, which do not include occupational medical assistance. To be included, patients must also consent for acquisition of medical records. Figure 1 presents the inclusion procedure, which has been effective since April 2012, when it was changed due to slow recruitment. Until then, patients were excluded in case of previous shoulder surgery and/or diabetes, if they were not in paid work for at least 25 hours per week, and if they were not fulltime sick-listed.

Participation in SIP is based on the principles of informed consent. Participants are covered by the Danish patient insurance system. SIP provides compensation for documented loss of earnings and transportation costs. The study has been approved by the Central Denmark Region Committees on Biomedical Research Ethics (identification number: M-20100131) and by the Danish Data Protection Agency (journal number: 2010-41-4316).

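### Occupational-intervention analyses adjust for centre only: baseline OSS and fear-avoidance scores go unused, and the two work outcomes have no baseline covariate in either comparison

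*Protocol article*

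**What the plan says.** The Statistical analyses section of the protocol article gives two covariate sets. Physiotherapy analyses are adjusted for centre, "for the occupational intervention (no, yes, irrelevant), and for the outcome measure at baseline". For the subgroup in paid work of at least 25 hours per week, a two-by-two factorial analysis focuses on the occupational main effect, "but cell-by-cell results will also be reported [22,23]; the analyses will be adjusted for centre". No other covariate is named for it.

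The outcomes concerned are these:

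- **Sickness absence percentage** (occupational primary at 3 months, physiotherapy secondary): hours of shoulder-related sick leave "in relation to the number of planned working hours within three months from baseline". On collection the article says: "This information is gathered by one month day-by-day calendars". In Table 1 the row "Shoulder-related sickness absence" is marked at 3 months only.
- **Transfer income percentage** (occupational primary at 12 and 24 months, physiotherapy primary at 24 months and secondary at 12): weeks on "health-related transfer incomes within 12 and 13–24 months from baseline, respectively, divided by 52 weeks". Table 1 marks it at 12, 16 and 24/28 months.
- **OSS**: at 3 months it "will be used as a secondary outcome measure for the occupational intervention to evaluate any deterioration", and it is again secondary for that intervention at 12 months. Table 1 marks it at baseline, 3 and 12 months.
- **Fear-avoidance beliefs**: secondary for both interventions at 3 and 12 months. Table 1 marks them at baseline, 3 and 12 months.

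The Participants section reports that until April 2012 patients were excluded "if they were not in paid work for at least 25 hours per week, and if they were not fulltime sick-listed"; this was then dropped. Randomisation is stratified by surgical department only.

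**The concern.** The same outcome, OSS, is baseline-adjusted in one comparison and not in the other, and no reason is given. The baseline score is on file for every randomised patient who completed the questionnaire, so the omission saves nothing and widens the confidence interval. Precision matters here because OSS serves the occupational comparison as a check for deterioration.

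The work outcomes raise a different problem. Both are totals that accrue after baseline, so neither has a baseline value of its own in the schedule. The physiotherapy rule nevertheless calls for one, and transfer income percentage is a primary outcome of physiotherapy at 24 months. The analyst would have to choose a substitute, or drop the term, after the data are in.

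Patients recruited before April 2012 had to be full-time sick-listed and later ones did not. Sick-leave status at entry can therefore be expected to vary and plausibly predicts later absence, yet neither the randomisation nor the occupational model takes account of it.

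**Working it through.** **1. The plan's own figure.** Inputs from Sample size calculations: 50 per arm, up to 10% dropout (45 analysed), SD 20, power 0.80, alpha 0.05 (two-sided assumed).

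- Normal approximation: 20 × √(2/45) × (1.960 + 0.842) = 11.81.
- Noncentral t with 88 degrees of freedom: 11.94.

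The stated 11.9 reproduces. It uses no baseline correlation, so the sample size agrees with a centre-only model.

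**2. OSS as an occupational secondary outcome.** Inputs: SD 9.0 and correlation 0.5 from Sample size calculations, where they are given for the physiotherapy comparison. Carrying them to the employed subgroup, with 45 per arm, is an assumption.

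- Unadjusted: 11.94 × 9.0/20 = 5.37 points.
- Residual SD after baseline adjustment: 9.0 × √(1 − 0.5²) = 7.79.
- Adjusted: 5.37 × √0.75 = 4.65 points.

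Residual variance falls by 25% and the detectable difference by about 13%. The effective sample rises by a factor of 1/(1 − 0.25) = 1.33. No correlation is given for fear avoidance, so its gain is not computed.

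**3. Work outcomes.** The article gives no correlation between any pre-baseline covariate and sickness absence or transfer income. The values of r below are assumed. Residual SD = 20 × √(1 − r²), 45 per arm, noncentral t with one further degree of freedom spent:

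| r (assumed) | Residual SD | Detectable difference (points) | Power at 11.9 | Effective sample factor 1/(1 − r²) |
|---|---|---|---|---|
| 0.1 | 19.90 | 11.9 | 80% | 1.01 |
| 0.2 | 19.60 | 11.7 | 81% | 1.04 |
| 0.3 | 19.08 | 11.4 | 83% | 1.10 |
| 0.5 | 17.32 | 10.3 | 90% | 1.33 |
| 0.7 | 14.28 | 8.5 | 97% | 1.96 |

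These figures are on the raw percentage scale. The plan foresees transforming outcomes where suitable, so the gain on the analysed scale may differ.

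**4. Is a covariate obtainable?** Work ability is marked at baseline in Table 1. Transfer income is counted in weeks from a national register. The Process evaluation section already plans to compute it for periods counted from surgery, and RCT baseline follows the postoperative control at 8–12 weeks. Weeks before baseline are therefore within reach, although the article does not list them as a baseline variable.

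**The case against.** The strongest reply is that the two covariate sets differ for a good reason: the occupational primary outcomes have no scheduled baseline value, so the physiotherapy adjustment could not simply be copied. That stands for sickness absence and transfer income. It does not explain the omission for OSS and fear avoidance.

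A second reply is that choosing further prognostic covariates is commonly left to an analysis plan, and that supplementary analyses with Table 1 variables are already foreseen. This has weight for the choice of a proxy. But the article does not stay silent on covariates: it states a set for each comparison, and the physiotherapy set calls for a term that two of its outcomes lack. One could read the factorial sentence as governing physiotherapy on the work outcomes too, which would remove that difficulty, but the article does not say so.

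Three stronger readings are tempting and not supported:

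- **That baseline data exist for the primary work outcomes.** Table 1 schedules none. A register value could be derived, but it is not planned.
- **That chance imbalance in sick-listing invalidates the primary result.** Randomisation keeps the centre-only estimate unbiased, and its standard error already allows for such imbalance. The article does not say how many entrants were sick-listed.
- **That the trial loses a third of its effective sample on sickness absence.** The 0.5 correlation is stated for OSS with itself. At 0.2 or below the gain is at most about 4%.

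Adding physiotherapy allocation to the occupational model is not pressed here, since a two-by-two factorial analysis ordinarily includes it.

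**Conclusion.** The point holds as an efficiency improvement together with a gap in wording. It is not an error of validity.

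- For OSS, and by the same reasoning fear avoidance, the occupational models omit a baseline value that is collected. The OSS cost is about 5.4 against 4.7 points in detectable difference, assuming that SD 9.0 and r = 0.5 carry over to the employed subgroup with 45 per arm.
- For sickness absence and transfer income, the physiotherapy baseline rule has no scheduled value to use, and this touches the 24-month physiotherapy primary outcome.
- A pre-baseline covariate for these two outcomes is obtainable and plausibly useful, given the April 2012 change in entry criteria. Its benefit cannot be fixed from the article: it ranges from almost nothing at r = 0.1 to a detectable difference of 8.5 points at r = 0.7.

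The stated power for the occupational comparison stands without any of this.

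**What to change.** 1. In the occupational models for OSS and fear-avoidance beliefs, add the baseline value of the same score.
2. For sickness absence and transfer income percentage, name in advance one baseline covariate and use it in both the occupational and the physiotherapy comparisons. Candidates are the number of weeks on health-related transfer income in a fixed register window before baseline, or baseline work ability.
3. Reword the physiotherapy rule so that it calls for the outcome at baseline where one is measured, and for the covariate in item 2 otherwise.

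These choices should be fixed before the outcome data concerned are examined. The article says that the 3-month physiotherapy analysis is already under way, so any change touching that analysis should be dated and reported as such. The cost is analysis wording and, if the register option is chosen, a slightly longer extract window. No new patient data are needed.
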